**Figure 1 F1:**
[figure not shown]
Study design and route-separated validation framework for AI-assisted CRS-R score standardization.

#### Inclusion criteria

2.2.1

Participants must meet all of the following criteria:

Age 18–80 years.Severe acquired brain injury based on clinical history, imaging, and presentation, including traumatic brain injury, hypoxic-ischemic encephalopathy after cardiopulmonary resuscitation, extensive intracerebral hemorrhage, or ischemic stroke.Clinical stability sufficient for bedside CRS-R assessment and routine scalp EEG recording.Behavioral diagnosis within the DoC continuum, including coma, UWS/vegetative state, MCS minus, or MCS plus, according to accepted neurological guidelines.Ability to complete two independent CRS-R assessments and one EEG recording within the protocol assessment window.Written informed consent provided by the legally authorized representative or immediate family member.Stable vital signs, absence of severe cardiopulmonary failure, and the ability to safely suspend continuous intravenous sedation within the assessment window when clinically permissible.

#### Exclusion criteria

2.2.2

Participants will be excluded if any of the following applies:

Persistent deep sedation, general anesthesia, or uncontrolled status epilepticus during the assessment window.Complete paralysis from severe cervical spinal cord injury or peripheral neuromuscular blockade that prevents interpretation of CRS-R motor or oral motor subscales.Severe irreversible neurodegenerative disease or severe psychiatric disorder that would confound DoC diagnosis.EEG dominated by uncontrolled epileptiform activity or status epilepticus, preventing valid resting-state background or connectivity feature extraction.EEG recordings of insufficient quality despite repeat acquisition when repeat acquisition is clinically feasible.Massive bilateral skull defects preventing accurate and symmetrical scalp electrode placement according to the international 10–20 system.Concurrent severe systemic infection or metabolic disorder causing an acute, reversible decline in consciousness.Refusal or withdrawal of informed consent by the legally authorized representative.

### Retrospective model development

2.3

The retrospective phase will establish the preprocessing pipeline, feature definitions, model architecture, missing-data rules, quality-control thresholds, and interpretability outputs before prospective enrollment begins. The model will be fully trained and locked before the first prospective participant is included.

#### Clinical contextual variables

2.3.1

Clinical contextual variables will be extracted from standardized electronic case report forms. These variables will include age, sex, etiology, time since injury, body position during assessment, tracheostomy or endotracheal tube status, mechanical ventilation, recent sedative exposure, antiseizure medication exposure, fever or active infection, metabolic derangement, recent seizures, severe motor impairment, aphasia or suspected language impairment, major visual or auditory limitation, and the time interval from recent acupuncture or neurorehabilitation intervention. The case report form will record the timing of CRS-R assessment, EEG acquisition, treatment sessions, nursing procedures, airway events, and clinically important changes in arousal state. These variables are included to account for known sources of behavioral score variability and to support reproducible covariate capture in prospective DoC research (32).

#### Sedation and medication handling

2.3.2

Sedation exposure will be documented before each CRS-R assessment and EEG recording. Continuous intravenous sedatives will include propofol, midazolam or other benzodiazepines, dexmedetomidine, opioid infusions, and other locally used sedative or analgesic agents. Intermittent sedatives, rescue analgesics, neuromuscular blocking agents, and antiseizure medications will be recorded separately. For each agent, the electronic case report form will capture current administration status, stop time when applicable, dose in the preceding 24 h, and administration within 6 h before the assessment episode.

CRS-R assessment and EEG acquisition will be attempted only when the treating team judges that temporary reduction or suspension of continuous sedation is clinically permissible. The target condition is absence of continuous intravenous sedative infusion during the behavioral assessment and EEG recording. Minimum target washout intervals will be 30 min after stopping propofol or dexmedetomidine infusions, 30 min after short-acting opioid boluses or infusion reduction, and 4 h after benzodiazepine bolus administration or midazolam infusion discontinuation when clinically permissible. Longer intervals will be recorded when hepatic or renal dysfunction, prolonged infusion, or delayed awakening is present. Antiseizure medications will not be withheld for study purposes; recent loading doses, rescue therapy, or major dose changes within 24 h will be recorded. Sedation depth will be recorded using the Richmond Agitation-Sedation Scale, FOUR score arousal observations, or the closest locally available structured arousal assessment. Cases with persistent deep sedation, general anesthesia, neuromuscular blockade that prevents behavioral interpretation, or major medication changes between paired ratings will be retained in feasibility summaries but excluded from prespecified sensitivity analyses when the change is judged to compromise CRS-R interpretability.

#### EEG acquisition and preprocessing

2.3.3

Routine scalp EEG will be recorded using the international 10–20 system with at least 19 channels. The minimum sampling rate will be 256 Hz, with higher sampling rates preserved when available. The target recording duration will be at least 20 min. The target analysis segment will be an eyes-open or resting unstructured bedside recording obtained without active command-following tasks. If eyes-open recording is not feasible, the observed eye state, arousal condition, recent stimulation, and nursing or respiratory events will be documented.

EEG preprocessing will use a prespecified locked pipeline: channel inspection, removal of non-physiological or disconnected channels, bad-channel interpolation when appropriate, band-pass filtering from 0.5 to 45 Hz, 50-Hz notch filtering when line noise is present, common average or linked-mastoid re-referencing according to the locked acquisition montage, artifact detection and rejection, and extraction of artifact-reduced analysis epochs. Quantitative analysis will use 4-s epochs with 50% overlap. The minimum analyzable duration will be 5 min of artifact-reduced EEG. Epochs will be rejected when any channel shows absolute amplitude greater than 500 μV, flat signal below 1 μV for at least 5 s, abrupt step change greater than 200 μV, visually confirmed electrode-pop or movement artifact, or high-frequency muscle contamination defined as 20–45 Hz power more than three standard deviations above the recording median. Recordings with more than 30% bad channels or less than 5 min of acceptable EEG after artifact rejection will be classified as quantitative-EEG failures. The final software implementation, reference montage, and quality-control log format will be archived with the locked preprocessing package before prospective enrollment.

Quantitative features will include regional and global relative band power, alpha-delta ratio, spectral entropy, Hjorth parameters, and connectivity metrics such as coherence or phase-based synchronization indices, depending on data quality. Exploratory feature engineering during retrospective development may include variational mode decomposition, sample entropy, spectral entropy, skewness, kurtosis, and weighted phase-lag index features (35, 36). Sleep-like EEG, low-arousal recordings, stimulation exposure, and EEG quality metrics will be retained as contextual or quality variables for feasibility and sensitivity analyses rather than silently excluded.

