#### Internal validation and model locking

2.3.5

During retrospective development, model performance will be assessed using nested fivefold cross-validation with patient-level splitting. If a patient contributes more than one assessment episode, all episodes from that patient will remain in the same fold. The inner loop will tune hyperparameters on the training partition, and the outer loop will estimate generalization performance on held-out patients. EEG preprocessing decisions that use data-derived thresholds, feature scaling, imputation, feature selection, dimensionality reduction, model selection, uncertainty thresholds, and score-shift review thresholds will be learned or fixed within the training partitions only and then applied to the corresponding held-out fold. Model parameters, preprocessing rules, feature definitions, missing-data handling logic, uncertainty thresholds, review thresholds, software versions, and deployment checksums will be archived before prospective use. No parameter updating, threshold tuning, or online learning will be allowed during prospective validation.

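### The 5-s flat-signal rule cannot be met inside a 4-s epoch, and the three-SD muscle rule may lose sensitivity as contamination rises; settle both before the pipeline is locked

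*Protocol article*

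**What the plan says.** All the rules at issue stand in one paragraph of Section 2.3.3 (EEG acquisition and preprocessing) of the protocol article.

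- Epoch length: "Quantitative analysis will use 4-s epochs with 50% overlap".
- Unit of rejection: "Epochs will be rejected when any channel shows absolute amplitude greater than 500 μV". The other criteria follow in the same sentence, so they too apply to epochs and to any channel. At least 19 channels are recorded.
- Flat signal: "flat signal below 1 μV for at least 5 s".
- Muscle: "high-frequency muscle contamination defined as 20–45 Hz power more than three standard deviations above the recording median".
- Recording length: "The target recording duration will be at least 20 min". A recording that keeps less than 5 min of acceptable EEG counts as a quantitative-EEG failure. Under Section 2.11 such a case may go to the report-level fallback.

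The paragraph lists artifact detection before epoch extraction, and re-referencing before both. It does not say whether flatness is tested on the continuous trace or within each epoch. It also does not say over which data the SD is taken, or whether it is a robust estimate.

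Section 2.3.5 closes the door on later correction: "No parameter updating, threshold tuning, or online learning will be allowed during prospective validation".

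**The concern.** Two stated durations do not fit together. The rule rejects 4-s units on a condition that needs at least 5 s of signal. If it is coded as written, it has no effect, and epochs with a flat channel reach the relative power, entropy and connectivity features. They also count toward the 5-min minimum that decides whether a recording is usable.

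The muscle rule raises a second, softer question. A limit built from the recording's own SD rises when contaminated epochs enter that SD, so the rule may weaken in the recordings that need it most. The Discussion expects EEG artifacts in this population. Both rules are to be locked before prospective enrollment, so the time to settle them is now.

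**Working it through.** The document gives no figure of its own on this point, so there is none to reproduce.

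**Flat rule.** Inputs from Section 2.3.3: epoch 4 s, step 2 s (50% overlap), limit 5 s, recording 20 min.

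1. Epochs in 20 min: (1200 − 4)/2 + 1 = 599.
2. Tested within an epoch, the longest possible flat run is 4 s, which is below 5 s. No epoch is rejected, whatever the length of the dropout. A 30-s flat run fully covers 13 to 14 epochs, since (30 − 4)/2 = 13, plus one when aligned with the grid. The rule removes none of them.
3. Tested on the continuous trace, with every overlapping epoch dropped, a 5-s run removes 4 to 5 epochs, since (5 + 4)/2 = 4.5. The rule then works.
4. A gap remains on the continuous reading. A flat run of length L, from 4 s to just under 5 s, escapes the limit and can fill a whole epoch. It fills at most one. For a random start the chance is (L − 4)/2, for example (4.9 − 4)/2 = 45%.

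**Muscle rule.** Assumptions not in the document: ordinary SD over all epochs of the same recording; a share p of epochs, below one half, raised by a constant d; baseline SD s; one channel.

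1. The median stays near baseline and SD = √(s² + p(1 − p)d²).
2. A contaminated epoch is flagged only if d > 3 × SD, that is p(1 − p) < 1/9 − (s/d)².
3. For very large d: p = (1 − √(1 − 4/9))/2 = 12.7%. For d/s = 10 the point is 11.4%, for 5 it is 7.7%, and for 4 it is 5.1%.
4. Simulation, one channel, 599 epochs, constant shift d/s = 10: contaminated epochs caught are 100% at p = 2%, 64% at 10%, 23% at 13% and 0.3% at 20%. With variable artifact power the decline is gradual: 22–35% at 13% and 14–16% at 20%.
5. Simulation with tenfold artifact power and lognormal background (log-SD 0.3 or 0.5, assumed):

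| Share contaminated | One channel | 19 independent channels, any-channel rule |
|---|---|---|
| 10% | 29–50% caught | 99–100% caught |
| 20% | 15–19% | 95–100% |
| 30% | 8–11% | 79–99% |

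Perfectly correlated channels return the one-channel column. A further set of scenarios, varying inter-channel correlation and the spatial extent of the artifact, gave 59–100% caught at 10% contamination and 20–89% at 30%.

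**Cost of a robust limit.** With median plus 3 scaled MAD, one channel and d/s = 10, detection is 100% up to 30% contamination and about 65% at 40%. False rejection of clean epochs was at most 1.7% in a one-channel simulation. Over 19 independent channels that becomes 1 − 0.983^19 = 28%. Across the scenarios tried, the loss of clean epochs ran from about 0 to 48%.

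**The case against.** The strongest reply has four parts.

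- **Order of steps.** Artifact detection is listed before epoch extraction, so the flat test may be meant for the continuous trace, where it works. This stands as a possible reading. A reader might infer that the rule is void in all circumstances; the document does not support that. Still, the sentence names the epoch as the unit rejected, and the 4-to-5-s gap survives. The listed order also puts re-referencing first. Under the common-average option a dropped channel then carries the negative of the channel average. With 19 independent channels of SD 15 μV (assumed) that is about 15 × √18/19 ≈ 3.4 μV, above the 1 μV limit. So the order does not clearly rescue the rule.
- **Other safeguards.** Disconnected channels are removed or interpolated earlier, and amplitude, step-change and visual criteria also apply. This limits the harm from persistently dead channels. None of these is stated to cover short dropouts. Run on the continuous trace, the residual gap is small: at most one fully flat epoch per run, out of about 599.
- **Muscle rule.** A reader might infer that the rule switches off at about 13% contamination and that heavily contaminated recordings pass as clean. Neither follows. The 12.7% is the one-channel limit for large, equal artifact. With variable artifact the decline is gradual, and rejection on any of at least 19 channels can restore most of the sensitivity. This part of the reply stands.
- **Detail held elsewhere.** Section 2.3 sets quality-control thresholds in the retrospective phase, and the final software is archived separately. That fairly covers the choice of SD estimator. It does not cover two stated numbers that conflict.

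**Conclusion.** The flat-signal point holds: as written, a 5-s condition cannot be met in a 4-s epoch. Applied per epoch, the rule rejects nothing. Applied to the continuous trace, it works except for runs of 4 to just under 5 s.

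The muscle point holds only conditionally. If the SD is the ordinary one over all epochs of the recording, sensitivity falls as contamination rises. The size depends on artifact strength, correlation between channels and the any-channel rule, none of which can be settled from the document. The simulated range is too wide for a single figure.

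The effect on the primary endpoint cannot be quantified. The pipeline that screens the development recordings is the one then locked for the prospective ones. Retained artifact would therefore add error to the AI score rather than invalidate its comparison with the reference. The correction is worth making because it is simple now and barred after lock.

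**What to change.** Before the preprocessing package is locked:

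1. Test flatness on the continuous signal and state the processing stage. Reject every epoch that overlaps a flat run, and set the duration limit no longer than the epoch. Alternatively, reject an epoch when more than a set share of it is flat.
2. State how the SD in the 20–45 Hz rule is computed, and check on the retrospective recordings whether masking occurs. If it does, use a robust spread or an absolute power cap. Choose the multiplier under any-channel rejection over at least 19 channels, so that a large share of clean epochs is not discarded. A reader might infer that a 3-MAD limit is a nearly free replacement; the 28% worked above shows why it must be tuned.

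The flat-rule change is a small edit to the code and the text. The muscle check needs an analysis of the retrospective recordings. The downside is somewhat more rejected epochs and possibly more recordings sent to the report-level fallback.

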#### Model architecture

2.3.4

The standardization system will use a two-stage multimodal architecture. In the first stage, six subscale-specific ordinal prediction modules will estimate probability distributions over the permissible score levels for each CRS-R subscale. In the second stage, a rule-constrained integration layer will assemble the AI-standardized subscale profile, compute the standardized total score, derive the diagnostic category, and estimate prediction uncertainty using locked ensemble dispersion or conformal uncertainty logic.

This structure replaces a simple total-score regression model because it better preserves CRS-R subscale structure and diagnostic rules. Extreme Gradient Boosting, random forest, support vector regression or classification variants, and related ensemble models may be evaluated during retrospective development. The final deployed model will be selected and locked before prospective validation.

#### Internal validation and model locking

2.3.5

During retrospective development, model performance will be assessed using nested fivefold cross-validation with patient-level splitting. If a patient contributes more than one assessment episode, all episodes from that patient will remain in the same fold. The inner loop will tune hyperparameters on the training partition, and the outer loop will estimate generalization performance on held-out patients. EEG preprocessing decisions that use data-derived thresholds, feature scaling, imputation, feature selection, dimensionality reduction, model selection, uncertainty thresholds, and score-shift review thresholds will be learned or fixed within the training partitions only and then applied to the corresponding held-out fold. Model parameters, preprocessing rules, feature definitions, missing-data handling logic, uncertainty thresholds, review thresholds, software versions, and deployment checksums will be archived before prospective use. No parameter updating, threshold tuning, or online learning will be allowed during prospective validation.

### Prospective clinical validation

2.4

The prospective phase will evaluate the agreement between AI-standardized scores and blinded expert reference scores in a real-world neurological rehabilitation workflow. During validation, the system will operate in read-only mode. It will not replace bedside CRS-R assessment and will not determine treatment allocation.

#### Rater training, standardization, and blinding

2.4.1

Bedside raters will be rehabilitation physicians or therapists who have completed structured CRS-R training before study initiation. Before formal enrollment, raters will complete a study-specific rater standardization phase including manual review, practice scoring, and pilot paired assessments in non-study cases. Raters must demonstrate substantial agreement during the pilot phase before participation.

For each participant, two bedside raters will be blinded to each other's scores and to AI output. EEG readers will be blinded to CRS-R scores and AI output. The adjudication committee will be blinded to rater identity, raw AI output, and model explanation results. The statistical team will analyze a de-identified dataset after database lock.

#### Assessment workflow

2.4.2

Each participant will undergo a prespecified assessment episode. The target workflow is completion of both CRS-R assessments and the EEG recording during the same morning block and before acupuncture, neuromodulation, or intensive rehabilitation sessions. The target interval between the two CRS-R assessments is no more than 2 h, and the target EEG timing is within 2 h before or after the midpoint of the paired CRS-R assessments. If target timing is not feasible, the maximum permitted interval will be 4 h between the two CRS-R assessments and 6 h between EEG and the paired CRS-R assessment window. Reasons for exceeding the target interval will be recorded. Sedation changes, fatigue, nursing care, airway events, acute complications, and rehabilitation sessions occurring within the assessment window will be recorded and used in sensitivity analyses.

The workflow will include:

Eligibility confirmation and consent from the legally authorized representative.Collection of baseline demographic and clinical contextual variables.First bedside CRS-R assessment by rater A.Second independent bedside CRS-R assessment by rater B, with a target interval of no more than 2 h and a maximum interval of 4 h after the first assessment.Routine scalp EEG, with a target timing within 2 h of the midpoint of the paired CRS-R assessments and a maximum timing within 6 h of the paired assessment window.Video recording of bedside behavioral assessments when consent and local policy permit.Offline AI inference using each rater's raw CRS-R subscale scores, EEG data, and clinical contextual data.Blinded expert adjudication to generate the standardized reference CRS-R score and diagnosis.

The order of raters will be alternated when operationally possible. Major medication, sedation, body-position, ventilatory, arousal-state, fatigue, nursing-care, treatment-session, or acute-complication changes between ratings will be documented. Participants with major instability between raters will remain in feasibility summaries and may be excluded from prespecified sensitivity analyses.

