### Statistical analysis

2.10

All analyses will be prespecified and performed after prospective database lock. The primary analysis population will include participants with two blinded bedside CRS-R assessments, usable EEG according to protocol, and an adjudicated reference score. A feasibility population will include all consented participants.

Baseline characteristics will be summarized as mean and standard deviation or median and interquartile range for continuous variables, and as counts and percentages for categorical variables. The primary analysis will summarize *D*_*i*_ and test whether the mean participant-level error reduction differs from zero using a paired test appropriate to the empirical distribution. A linear mixed-effects model with participant as a random effect and method and rater as fixed effects will be used as a secondary sensitivity analysis to estimate rater-level effects. Intraclass correlation coefficients, mean absolute error, root mean square error, and Bland-Altman plots will be reported with 95% confidence intervals.

Diagnostic-category agreement will be assessed with weighted kappa, macro-averaged F1-score, sensitivity, specificity, and confusion matrices using the mapping rules in Table 1. Subscale-level performance will be assessed using ordinal agreement metrics, weighted kappa, and subscale-specific absolute error. Inter-rater variability before and after AI-assisted standardization will be compared using paired tests and mixed-effects models. The uncertainty module will be evaluated by testing whether high-uncertainty cases are enriched for large scoring error, rater disagreement, or reference-standard disagreement.

Confidence intervals for primary and major secondary metrics will be estimated using participant-level bootstrap resampling. Prespecified subgroup analyses will explore model performance across etiology, chronicity, tracheostomy status, severe motor impairment, and recent sedative exposure. Sensitivity analyses will exclude participants with substantial clinical changes between ratings, cases exceeding target timing windows, and cases with major sedation or airway changes during the assessment episode. A reduced-feature inference mode using report-level EEG variables only will also be tested.

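### Rater order is alternated only when convenient and the secondary mixed model has no assessment-order term, so its rater effect can absorb a first-versus-second shift if order becomes unbalanced

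*Protocol article*

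**What the plan says.** The step list in section 2.4.2 of the protocol article reads "First bedside CRS-R assessment by rater A", then "Second independent bedside CRS-R assessment by rater B". The target gap is no more than 2 h; failing that, "the maximum permitted interval will be 4 h between the two CRS-R assessments". The paragraph after the list adds: "The order of raters will be alternated when operationally possible". It gives no balance target and no rule for what happens when alternation is not possible.

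Section 2.10 specifies "A linear mixed-effects model with participant as a random effect and method and rater as fixed effects", to be used "as a secondary sensitivity analysis to estimate rater-level effects". No order or period term is named.

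Three other sections bear on the point. Section 2.3.1 has the case report form record when each CRS-R assessment takes place. Section 2.5 sets the reference at the highest credible response across both assessments and the supporting records. Section 2.7 builds the primary D_i by averaging raw-minus-AI error over the two raters of each participant.

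**The concern.** The two ratings of a participant differ in who rates and in when. A model with a rater term and no order term can separate the two only if each rater goes first about equally often. The alternation rule aims at this but does not secure it, because it yields to operational convenience and convenience may be systematic: one rater may usually be the one free earlier in the morning.

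A first-to-second shift is plausible on the protocol's own account. Section 2.4.2 foresees changes in fatigue, arousal, nursing care and sedation between ratings. Because the reference is the best credible response over both visits, a general fall or rise in responsiveness would leave one position further from the reference than the other. With unbalanced order, that difference would be reported as a difference between raters.

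At stake is the interpretation of one coefficient: whether raters differ in accuracy, or patients differ between the first and second visit.

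**Working it through.** The plan states no figure on this point, so there is none to reproduce.

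**Inputs.** Order rule: section 2.4.2. Model terms and purpose: section 2.10. Not given in the document, and therefore treated as assumptions: q, the share of participants seen first by rater A, and d, the mean second-minus-first shift in absolute error. For simplicity the same two people are taken to rate everyone.

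**Bias without an order term.** Let r be the true B-minus-A difference.

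- A first (share q): the expected B-minus-A difference is r + d.
- B first (share 1-q): it is r - d.
- Average: q(r + d) + (1-q)(r - d) = r + (2q-1)d.

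The bias is therefore (2q-1)d.

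**Cost of adding the order term.** The rater and position codes then have correlation 2q-1, so the standard error of the rater effect is multiplied by 1/√(1-(2q-1)²). At q = 0.7 this is 1/√(1-0.16) = 1.09. At q = 0.8 it is 1/√(1-0.36) = 1.25.

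| q | Bias as share of d | Bias if d = 0.3 | Bias if d = 0.5 | SE factor with order term |
|---|---|---|---|---|
| 0.5 | 0% | 0.00 | 0.00 | 1.00 |
| 0.6 | 20% | 0.06 | 0.10 | 1.02 |
| 0.7 | 40% | 0.12 | 0.20 | 1.09 |
| 0.8 | 60% | 0.18 | 0.30 | 1.25 |
| 0.9 | 80% | 0.24 | 0.40 | 1.67 |
| 1.0 | 100% | 0.30 | 0.50 | not estimable |

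Bias is in CRS-R points of absolute error. The values 0.3 and 0.5 for d are illustrations only.

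**Simulation check.** 2,000 runs with 98 participants, true rater effect 0, method effect 1.0 and d = 0.5. Without an order term the mean rater estimate was 0.000 at q = 0.5, 0.101 at 0.6, 0.296 at 0.8, 0.395 at 0.9 and 0.501 at 1.0, in line with the formula. With an order term it was within 0.006 of zero at every q below 1. The method effect stayed between 0.995 and 1.004 throughout.

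**What is not affected.** Raw and AI errors for a given rating share the same rater and the same occasion, so an additive order shift cancels from raw minus AI. D_i averages over both ratings and does not depend on which is labelled A. V_i is an absolute difference between the two ratings, so swapping labels leaves it unchanged. V_i does mix rater and occasion differences within a participant, but neither alternation nor an order term in this model would alter that.

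**The case against.** The strongest reply is that this is analysis-plan detail for a secondary sensitivity model in a condensed article. A separate plan may add an order term, and the recorded assessment times would allow it. The protocol also limits drift: both ratings are targeted to one morning block before intensive treatment, and sensitivity analyses drop participants with substantial changes between ratings or exceeded timing targets. All of this is true and keeps the point small. It does not remove it. The article does state the model's terms and purpose, ordinary drift survives those exclusions, and balance of order is a matter of conduct that no later analysis can restore if alternation largely fails.

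The objection is also right on the figures. q and d are assumed. The formula presumes one fixed pair of raters, whereas section 2.4.1 requires two raters per participant without fixing a pair. With a pool of raters, what matters is how often each person goes first.

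A reader might infer from the step list that order is fixed as A then B, so that confounding is complete. The text does not support this: the same section plans alternation, and alternating the order of raters makes most sense if A and B are people. The q = 1 row is a limiting case, not the plan. Nor does the text support a claim that predictable alternation biases scoring, since raters are blinded to each other's scores and to AI output.

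**Conclusion.** The point holds as a minor one. The rater effect in the secondary mixed model is free of a first-versus-second component only if order is balanced, and the wording does not guarantee balance. The bias is (2q-1)d. Under balanced alternation it is nil. At a moderate imbalance of q = 0.7 to 0.8 it is 40% to 60% of whatever shift exists. Whether this will matter in practice cannot be judged from the document, which gives neither quantity.

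A reader might go on to doubt the primary result. The documents give no ground for that, because the primary comparison is made within each rating.

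**What to change.** In section 2.10, define rater by coded identity, derive first or second position from the assessment times already recorded, and add assessment order as a fixed effect alongside method and rater. Report the first-versus-second difference separately from the rater effect.

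In section 2.4.2, make balanced alternation of rater order the default, log departures, and report the order actually used. Randomised blocks would also serve but are a preference: balanced alternation already brings the bias to zero.

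The cost is a few sentences and a departure log, with no added assessments or participants. The downside is a wider interval for the rater effect when order is unbalanced: about 9% on the standard error at q = 0.7 and 25% at q = 0.8, with no penalty at q = 0.5. If order never alternates, rater and order cannot be separated by any model, so the change in 2.4.2 should be made before enrolment.
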